Another possibility is that screening alone might not be sufficient to induce improvements in risk factors, thereby limiting its ability to subsequently reduce clinical outcomes, which would suggest the need for more intense interventions. For example, one meta-analysis of health promotion interventions aimed at behavior change found that although such interventions do not reduce cardiovascular events in general populations, they might be effective in certain risk groups, i.e., people with hypertension and T2D [11]. Similarly, another meta-analysis of health promotion interventions targeting risk groups, in this case people living in low- and middle-income settings, suggested beneficial effects on some surrogate measures such as blood pressure. Yet, heterogeneity was substantial and there was not enough evidence to determine the effect on cardiovascular events and lifestyle habits [12], lending the authors to request further trials.

In Sweden, a prevention program has been developed in primary care since the mid-1980s [13, 14]. The program includes systematic screening of T2D and CVD risk factors followed by a person-centered lifestyle health dialogue based on the individual risk profile. The screening assessment includes questionnaires assessing a wide range of factors including medical history, medications, general health, mental health, heredity, living situation, quality-of-life, and lifestyle habits as well as blood tests of biological risk factors, blood pressure measurement, and anthropometric measurements. A recent systematic review suggested that the Swedish prevention program reduces all-cause mortality, cardiovascular mortality, blood pressure, cholesterol, blood glucose, waist circumference, and body mass index, while positively influencing dietary habits [15]. No effects of the program were detected for physical activity, tobacco use, and alcohol consumption. It should, however, be noted that the quality of the underlying evidence ranged from low-to-moderate, and six out of seven studies included in the review were observational. Moreover, the Swedish program has neither been implemented or evaluated in settings specifically targeting socioeconomically disadvantaged settings nor has it been compared to other preventive interventions. This would be important given the typically lower participation rates observed in these areas [16].

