The specific aims of this trial are to evaluate the following: (I) the long-term effects on T2D and CVD incidence and mortality among participants receiving HDI as compared to participants receiving OS; (II) the short-term effects on biological risk factors (blood pressure, cholesterol levels, glucose levels, body mass index) and health-related quality-of-life (HRQoL), among participants receiving HDI as compared to participants receiving OS; (III) the short-term effects on lifestyle habits (tobacco/nicotine usage, dietary habits, alcohol consumption, physical activity), among participants receiving HDI as compared to participants receiving OS; (IV) the potential effect modification by sex, socioeconomic status, and birth country, for all of the above; (V) the differences in resource use and associated costs between HDI and OS in the short and long terms; (VI) the costs per quality-adjusted life year (QALY) and per blood pressure target attained associated with HDI as compared to OS in the short term; and (VII) the cost per life year gained associated with HDI as compared to OS in the long-term.

Additionally, we will assess various implementation and process outcomes, including (I) the number of invited PCCs that agree to participate; (II) the adherence to the original intervention protocols by healthcare professionals; (III) the perceived acceptability, appropriateness, and feasibility of implementing the interventions among healthcare professionals; (IV) the barriers and facilitators for implementation of the interventions among healthcare professionals; (V) the proportion of patients choosing to participate among those invited and the reasons for declining participation among non-participants; (VI) the representativeness of participants as compared to the total eligible population based on socioeconomic characteristics; (VII) the case-finding rates, defined as the proportion of participants among whom elevated levels of biological risk factors are detected for the first time; and (VIII) the estimated time needed to treat (TNT).

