### Sample size

Sample size calculations were based on change in systolic blood pressure as the main outcome measure. We considered a 5-mmHg reduction in systolic blood to be clinically relevant as meta-analyses of randomized trials show that such a reduction can reduce the risk of CVD by about 10% regardless of CVD history, including among people with normal to high-normal blood pressure [22], as well as specifically in middle-aged adults [23].

Based on systolic blood pressure data in Stockholm Region that were obtained from electronic medical records, the estimated variance of systolic blood pressure levels between PCCs (clusters) was equal to 2, and the variance between subjects within PCCs (individuals) was equal to 256. These settings give rise to the underlying variance structure of the data, essential for sample sizes calculations, namely a difference of 5 mmHg in systolic blood pressure between arms (VA = 12.5), variance between clusters, (VC = 2), and variance between individuals within PCCs (VE = 256). We calculated the number of clusters, the number of individuals, and the power of the sample using various combinations of VA, VC, and VE values close to those outlined above. For each calculation, we adjusted one parameter while holding the other two constant. We used the package clusterPower version 0.7.0 [24], R Statistical Software version 4.1.3 [25], for the sample size and/or power calculations for the different variance settings.

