Accordingly, we calculated that based on 15 clusters in each arm, a minimum of 840 participants (*n* = 420 in each arm and *n* = 28 per cluster) would yield 80% power to detect a reduction of 5 mmHg systolic blood pressure in the HDI group as compared to OS. Rising power to 90% while keeping the number of clusters to 15 per arm would require a minimum of 1200 participants (*n* = 600 in each arm and *n* = 40 per cluster). Additionally, anticipating difficulties with cluster recruitment and retention, we also calculated that if the size of the cluster is increased to *n* = 69, a power of 80% would be obtained with 9 clusters per arm, and 90% power would be obtained with 11 clusters per arm. Because we expected difficulties with recruitment of PCCs and participant recruitment within PCCs, as well as subsequent attrition of the two, the goal was to recruit at least 30 PCCs (*n* = 15 in each arm) in Stockholm Region, each of which will aim to recruit *n* = 100 participants, yielding a maximum total study population of *N* = 3000.

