### Long-term health outcomes and resource use

To examine the effect on long-term health outcomes, cases of incident T2D and CVD (ischemic heart disease and stroke) and deaths due to T2D and CVD will be collected during 5 and 10 years of follow-up from regional and nationwide health registers, using International Classification of Diseases, 10th revision (ICD-10) codes E11 for T2D and I00-I99 for CVD. The registers that will be used are the National Patient Register, the National Cause of Death Register, the National Diabetes Register, and the Stockholm Regional Healthcare Data Warehouse. The National Patient Register includes data on all inpatient care in Sweden with 100% coverage since 1987, and since 2001, it also includes data on specialized outpatient care [35]. The Cause of Death Register covers data on all deaths in Sweden since 1952 [36]. Both of these registers are managed by the National Board of Health and Welfare. The National Diabetes Register was initiated in 1996, has 87% coverage, and includes data on patients with a diagnosis of diabetes, regardless of the care provider, thus including also primary data in contrast to the National Patient Register [37, 38]. This register is managed by Register Centre, Västra Götaland, Sweden. The Stockholm Regional Healthcare Data Warehouse (VAL) is a regional database including data on diagnoses and healthcare utilization from inpatient, specialized outpatient, and primary care for all people living in Stockholm Region since 1997 [39]. The coverage is complete since 2013 [37]. Additionally, information on prescribed medications for T2D and CVD (at baseline and during follow-up) will be collected from the Prescribed Drug Register using Anatomical Therapeutic Chemical codes A10, C02-C03, C07-C10. The Prescribed Drug Register is managed by the National Board of Health and Welfare and includes data on all prescribed medications that are collected at Swedish pharmacies since July 2005 [40]. Cost data will be collected from regional pricelists, the Cost Per Patient database, held at the Swedish Association of Local Authorities and Regions, and the national pricelist of reimbursed medications, held at the Dental and Pharmaceutical Benefits Agency.

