#### Health economic evaluation

For the short-term health economic evaluation, a healthcare costing perspective will be used, including utilization of healthcare in primary, specialized outpatient, and inpatient care as well as medication. Data from the VAL database will be used for this analysis. Total health resource use and associated costs in each arm will be accumulated and analyzed over the 12-month follow-up. Net costs, which is the difference between intervention costs and total health resource use of participants, will thereafter be estimated for both arms. Total QALYs at 6 and 12 months in each arm will be calculated by using the area under the curve method [51]. Incremental differences in QALYs and costs between participants in the HDI and OS arm at 6 and 12 months will be assessed using GLM models with gamma distribution for cost outcomes and gaussian for QALYs. Logistic regression analyses will be used for estimating between-group differences in persons with blood pressure target attained. Between-group differences in healthcare costs will be analyzed while controlling for baseline costs, while baseline utilities will be controlled for in analyses of accumulated QALYs between groups. The cost per QALY and per blood pressure target attained will be assessed using the incremental differences between the groups at 12 months.

For the long-term assessment of cost-effectiveness, total healthcare resource use and its associated costs will be accumulated and analyzed over the 5- and 10-year follow-up period, employing the same data source (VAL) and analytical framework (GLM) as for the short-term assessment. Intervention costs will also be used in this evaluation for the estimation of net costs. Incident cases of T2D and CVD will similarly be accumulated over the follow-up period, and incremental differences at 5 and 10 years will be assessed using logistical analyses. The total costs and health outcomes will be analyzed in a cost-consequence analysis. Furthermore, accumulated deaths due to T2D and CVD over the 5- and 10-years follow-up will be used to assess incremental life years gained between the two groups, and this outcome measure will consecutively be used in a cost-effectiveness analysis estimating the cost per life years gained. Probabilistic sensitivity analyses will be employed throughout the short- and long-term analyses to account for parameter uncertainty.

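### Incremental life years gained are derived only from T2D and CVD deaths, although the aim is an unqualified cost per life year gained and the costs are total healthcare costs

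*Protocol article*

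**What the plan says.** All references are to the protocol article. Specific aim VII under Objectives is "the cost per life year gained associated with HDI as compared to OS in the long-term", with no restriction to particular causes of death. Health economic evaluation fixes the denominator: "accumulated deaths due to T2D and CVD over the 5- and 10-years follow-up will be used to assess incremental life years gained". The same paragraph fixes the cost side: "total healthcare resource use and its associated costs will be accumulated and analyzed over the 5- and 10-year follow-up period". Those costs are not limited to T2D or CVD care.

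Long-term health outcomes and resource use lists only cause-specific mortality: "deaths due to T2D and CVD will be collected during 5 and 10 years of follow-up from regional and nationwide health registers". Statistical analysis plans a mixed-effect Cox model for T2D and CVD incidence and mortality. No all-cause mortality outcome is planned anywhere in the article. The data source would allow one: "The Cause of Death Register covers data on all deaths in Sweden since 1952".

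The text does not say how participants who die of another cause enter the life-year calculation.

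**The concern.** The denominator is narrower than the aim it serves. It also does not match the numerator: the cost of treating other diseases counts, but deaths from those diseases do not. This is a stated rule, not a detail left for a later document.

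Other-cause mortality could differ between arms in three ways, with different consequences.

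- **An intervention effect.** The intervention targets smoking, alcohol, diet and physical activity, so an effect on other deaths is possible. The Background cites a review suggesting that "the Swedish prevention program reduces all-cause mortality, cardiovascular mortality, blood pressure". Leaving out such an effect biases the ratio.
- **Chance.** Leaving out chance differences does not bias the ratio, but it makes the interval narrower than the real uncertainty about life years.
- **Selection.** HDI centers invite enlisted patients alphabetically. OS centers enroll people who attend for another reason, and exclude appointments for hypertension, T2D and CVD. The Discussion accepts that some selection bias will probably remain, in an unpredictable direction.

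At stake is the long-term cost-effectiveness figure, in a trial meant to inform decisions on scaling up the program.

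**Working it through.** The article gives no mortality rate, life-year figure or cost ratio, so there is nothing to reproduce. The following is an illustration.

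**Inputs from the article.** The planned maximum is 3000 participants, taken as 1500 per arm. For the effect, Sample size says of a 5 mmHg reduction that "such a reduction can reduce the risk of CVD by about 10% regardless of CVD history". I apply a hazard ratio of 0.9 to T2D/CVD death; the step from CVD risk to death is an assumption.

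**Assumed inputs, not in the article.** Constant hazards. T2D/CVD death at 0.5, 1 or 2 per 1000 person-years, other-cause death at 2, 3 or 6 per 1000, and a hazard ratio for other-cause death from 0.90 to 1.10. The central case is 1 and 3 per 1000.

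**Formulas.** With total hazard h, restricted mean survival to T is R(h) = (1 - exp(-hT))/h. The all-cause gain per 1500 is 1500 × [R(HDI) - R(OS)]. The cause-specific gain can be read in two ways:
- Other-cause deaths are censored: 1500 × [R(0.0009) - R(0.001)].
- Other-cause deaths are counted as alive to T: 1500 × the arm difference in L, where L = h1 × [T/h - (1 - exp(-hT))/h²] and h1 is the T2D/CVD hazard.

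**Central case, T = 10 years.**
- Cause-specific, censored: 1500 × (9.95513 - 9.95017) = 7.45.
- Cause-specific, counted as alive: 1500 × (0.04934 - 0.04442) = 7.38.
- All-cause, other-cause HR 1.00: 1500 × [R(0.0039) - R(0.004)] = 1500 × (9.80751 - 9.80264) = 7.31.
- All-cause, other-cause HR 0.95: 1500 × [R(0.00375) - R(0.004)] = 1500 × (9.81482 - 9.80264) = 18.27.
- All-cause, other-cause HR 1.05: 1500 × [R(0.00405) - R(0.004)] = 1500 × (9.80021 - 9.80264) = -3.65.

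The cause-specific figure hardly moves across the last three rows (7.35 to 7.41 counted as alive, 7.45 censored). At HR 0.95 the all-cause gain is about 2.5 times as large (18.27/7.38); at HR 1.05 it has the opposite sign.

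**Whole grid, equal other-cause mortality, 5 and 10 years.** The cause-specific increment exceeds the all-cause one by about 0 to 2% if other-cause deaths are counted as alive, and by about 0.5 to 4% if they are censored.

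**How large is a 5% difference?** Expected other-cause deaths per arm over 10 years are 1500 × (0.003/0.004) × (1 - exp(-0.04)) = 44. Five percent is about 2 deaths. The standard deviation of the arm difference from chance alone is about √(44 + 44) = 9 deaths.

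**Effect on precision.** If deaths are uniform over 10 years, the mean squared years lost per death is 100/3 = 33.3. Ignoring clustering, the standard error of the arm difference is about √(deaths in both arms × 33.3). The central case has about 28 T2D/CVD deaths and 116 deaths in all: √(28 × 33.3) = 31 against √(116 × 33.3) = 62 life years. With 6% ten-year mortality in 3000 and a 25% T2D/CVD share (45 of 180 deaths), it is 39 against 77. The ratio is √(1/share), so it doubles at a 25% share.

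**The case against.** The strongest reply is that a cause-specific denominator is a deliberate trade of completeness for precision. The intervention aims at T2D and CVD, other deaths are mostly noise, and including them roughly doubles the standard error while the expected gain is only about 7 life years per 1500. If other-cause mortality is equal, almost nothing is lost. A 5% difference is about two deaths per arm, well within chance. Differences due to unequal recruitment are not treatment effects, and an all-cause measure would bring them in. The cited all-cause benefit could come entirely from cardiovascular deaths, and the Background itself calls that evidence low to moderate in quality and mostly observational.

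Much of this stands. It limits the claim to a possible bias of unknown size and direction. It does not justify the exclusion. The wider interval is the real uncertainty of a life-year estimate, and the planned probabilistic sensitivity analysis cannot restore deaths that the calculation leaves out. Selection is a reason for covariate adjustment, which the article already plans for its outcome analyses, and it can affect T2D/CVD deaths as well.

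A reader might infer three stronger points that the article does not support.

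- **That people who die of other causes are credited with survival to year 5 or 10.** The text does not say so, and censoring at death is equally possible.
- **That life years cannot be computed because only accumulated deaths are named.** The planned Cox model already needs event times, so dates of death will be available.
- **That the error equals all life years lost to other causes.** That is a gross total over both arms; the plan uses the increment, in which most of it cancels.

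**Conclusion.** The point holds in limited form. The article bases incremental life years on T2D and CVD deaths alone, which does not match its unqualified aim or its total-cost numerator. The ratio may be biased when other-cause mortality differs systematically between arms, and its interval is too narrow in any case. The increment is off by only a few percent if other-cause mortality is equal. It can be off by a factor of about 2.5, or have the wrong sign, if other-cause mortality differs by 5%. These sizes rest on assumed death rates, constant hazards, a hazard ratio of 0.9 for T2D/CVD death and the maximum sample of 3000; none is an estimate for this trial.

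That aim VII cannot be answered, or that the ratio is certain to be wrong, is not shown. The point concerns one long-term economic result and does not touch the primary outcome.

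**What to change.** In Health economic evaluation, define life years per participant from the date of death from any cause, taken from the Cause of Death Register and censored at emigration. Estimate restricted mean survival to 5 and 10 years by arm, with the planned covariate adjustment and allowance for clustering by primary care center, and use that difference in the cost per life year gained. Keep the T2D/CVD-death version as a labelled sensitivity analysis, stating how deaths from other causes are handled in it. T2D and CVD mortality stay as clinical outcomes.

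The cost is a change of wording plus use of all-cause death dates from a register already in the plan. The 5- and 10-year analyses come well after short-term data collection ends (planned for December 2025), so there is time. There are two real downsides. The interval widens, with a standard error about double on the assumed death counts. An all-cause difference may also partly reflect post-randomization selection, which adjustment may not fully remove and which should be stated when the ratio is reported.

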### Data collection and data management

All clinical assessments at baseline and at 6 months and 12 months post intervention are performed by the healthcare professionals involved in the trial at each of the PCCs, except for the blood sampling which, as described earlier, will be performed by staff at the accredited laboratories associated with the PCCs. To meet the diversity of language among participants, the questionnaires will be available in Swedish, English, Arabic, Turkish, Somali, Tigrinya, Russian, Spanish, and Dari. Additionally, for participants belonging to PCCs randomized to HDI, and who have language barriers, it will be possible to have assistance from an interpreter during the health dialogue.

Because the clinical data will be collected as part of the pilot program at the PCCs, it will be stored in the patients’ electronic medical records as per routine procedures. The data from the patients’ electronic medical records will be integrated with the register-based data, as well as the manually entered survey data, and stored securely on servers at the Centre for Epidemiology and Community Medicine, Stockholm County Health Care Area, Region Stockholm, where only authorized researchers will have access. A member of the research team will perform range checks of the data. The physical consent forms will be stored securely at the PCCs according to standard safety procedures, and the information will also be entered manually into a database and stored securely on servers at the Centre for Epidemiology and Community Medicine, Stockholm County Health Care Area, Region Stockholm.

### Data retention plan

Members of the research group will provide updates on the trial status to the healthcare professionals at the PCCs who participate in the trial. Moreover, the healthcare professionals will provide all study participants with a reminder of their scheduled assessment ahead of each assessment (baseline, 6-month follow-up, 12-month follow-up). Participants who miss their assessment will be given the possibility to reschedule. For the assessment of long-term health outcomes, loss to follow-up should be minimal thanks to the use of high-coverage registers.

### Confidentiality of data

All data will be handled in accordance with Swedish law and the EU General Data Protection Regulation. The data will be stored securely on servers at the Centre for Epidemiology and Community Medicine, Stockholm County Health Care Area, Region Stockholm, where only authorized researchers will have access. The data will be pseudo-anonymized and analyzed and presented only at an aggregated level; hence, data for specific individuals will not be presented. The data protection officer of Stockholm County Health Care Area is also the data protection officer of this study.

### Dissemination of results

The results will be presented in written format through reports issued by the Centre for Epidemiology and Community Medicine, Region Stockholm, as well as through scientific articles in peer-reviewed journals. Verbal dissemination will occur through presentations at internal and external meetings as well as through conferences.

